#### Control group

In this first visit, the initial tests of control group must be answered. These tests include two sociodemographic questionnaires: a) about the caregiver – sex, birthdate, nationality, marital status, level of studies, health problems; and b) about caretaker – type of caretaker, birthdate and sex of the patient, his/her illness, hours of care, relationship between them, helpers in caregiving and emotions related on caregiving. It also includes the scale of positive mental health by Lluch [16], and the caregiver burden [13]. Both instruments will be used in visit 2 and 3.

#### Experimental group

The experimental group has to answer questionnaires and scales as well as the control group. Besides, there is one extra questionnaire for visit 1 and visit 2. In visit 1, there is a questionnaire about the usage of technology. And in visit 2, a questionnaire about the app satisfaction.

### Follow-up

The intervention through the app does not have any direct follow-up. Nevertheless, when the caregiver gets a negative outcome from one of the smartphone app activities, the app addresses the caregiver to visit his/her nurse.

### Outcomes

The primary outcome will be a change in positive mental health and caregiver burden at the first, third, and sixth month in the experimental group, compared to the control group.

The secondary outcome will be related to the adherence and satisfaction with the app: a) adherence to the intervention, measured by frequency of using the app; b) satisfaction with activities by the responses of usefulness of each activity; c) satisfaction with smartphone app in general reported by the satisfaction questionnaire.

### Statistical analysis

The data will be analysed with SPSS version 22.0 (IBM CORP., Armonk, NY). Both groups results are going to be described by a descriptive analysis. Quantitative variables with a normal distribution will be described as means and standard deviation, or median and interquartile range otherwise, and qualitative variables as percentages and 95% confidence intervals. Possible baseline differences between trial arms will be statistically tested and further analyses will be adjusted for imbalances in the baseline scores. The primary analysis will be by intention to treat. For the primary outcomes, analyses will be corrected for multiple testing.

As sensitivity analyses, completers of all assessments will be analysed separately. Hypotheses tests will be performed at *α* = 0,05. The numeric outcomes will be analysed using analyses of variance; categorical outcomes will be analysed using *χ*^2^-tests.

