### Sample size

Sample size was calculated considering to an alpha risk of 0,05 and beta risk of 0,2. Considering that, to get evidential data of the results, the sample should be of 54 subjects in each group with an estimated loss of 30% during follow-up and recognizing as statistically significant a difference greater than or equal to 10.

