## Discussion

This study will evaluate whether positive mental health improves, and burdens of care reduces on caregivers. One strength of this study is its robust design and follow-up assessment allowing the evaluation of long-term effects of the intervention. However, one of its limitations is its open design. The intervention cannot be masked; both patients and nurses in the experimental and control group will be aware that they are participating in a positive mental health intervention. This could affect to the success or failure of the intervention and could introduce bias. Randomization has been considered to help achieving a balance in sociodemographic, as well as risk factor profile. A blinded researcher will be in charge of analysing the data.

Among the strengths of the study, there is that this clinical trial has the potential to provide a validated tool to use with caregivers. A tool which could be useful to increase positive mental health. This could benefit the caregiver and even the caretaker. In addition, it has potential to decrease burdens of care. If its effectiveness is proved, this tool can be adapted to multiple frameworks.

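### Adjustment for the baseline score is made to depend on a test of baseline differences; it should be prespecified for every primary comparison

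*Protocol article*

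**What the plan says.** The Statistical analysis section of the protocol article gives a two-step rule: "Possible baseline differences between trial arms will be statistically tested and further analyses will be adjusted for imbalances in the baseline scores". The only model it then names for the two scales is a plain one: "The numeric outcomes will be analysed using analyses of variance". Nowhere is the baseline score made a covariate unconditionally.

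Other relevant statements in the article:

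- **Outcomes** defines the primary outcome as change in positive mental health and in caregiver burden, compared between arms at months 1, 3 and 6.
- **Data collection** has both scales completed at visit 1 in both arms, so the covariate will be in hand.
- **Screening and randomization** allocates individual caregivers 1:1 with a software-generated sequence.
- **Sample size** gives an "alpha risk of 0,05 and beta risk of 0,2", a difference of 10, 30% loss and 54 per group. It gives no SD and no correlation between baseline and follow-up.

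**The concern.** Under proper randomisation every baseline difference is due to chance, so a 5% test of it will be significant in about 5% of trials, however important or unimportant the variable is. The benefit of adjusting depends on how strongly the baseline score predicts the later score, and the test does not measure that. A rule that lets the test choose the model therefore adjusts on the wrong grounds. It also leaves the primary model unsettled until the data are seen.

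Two things are at stake. One is precision, in a trial that plans for 80% power and expects to lose 30% of its participants. The other is validity given the trial actually obtained: when the imbalance is sizeable but falls short of the trigger, the comparison goes ahead without adjustment, and its error rate is not the nominal one.

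**Working it through.** **Inputs from the article.** Alpha 0.05, power 0.80, difference 10, 54 per group, 30% loss, 1:1 allocation.

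**Assumed, because not stated.** Two-sided testing; SD; baseline-to-follow-up correlation ρ; a 5% trigger for the baseline test; about 38 analysed per arm (54 × 0.7 = 37.8).

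**Step 1: the plan's own figure.** With no SD given, 54 per group can be neither confirmed nor refuted. Solving for the SD, with 2.802 = 1.960 + 0.842:

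SD = 10 × √(n/2) / 2.802 = 10 × √(37.8/2) / 2.802 = 15.5.

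Running it forward, n = 2 × (2.802 × 15.5/10)² = 37.7, so 38 completers, and 38/0.7 = 54.3, so 55 randomised, one more than stated. Other routes to 54 imply other SDs: 16.3 if loss was added as n × 1.3, 17.5 if one-sided, 18.5 if no loss was allowed for. The check below uses 15.5.

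**Step 2: power by formula.** Power = Φ(10/SE − 1.96), where SE = SD* × √(2/38). SD* is 15.5 for follow-up scores, 15.5 × √(2(1 − ρ)) for change scores and 15.5 × √(1 − ρ²) for ANCOVA. For example, at ρ = 0.5:

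- Follow-up score: SE = 3.556, power = Φ(2.812 − 1.96) = 80.3%. The change score has the same SD at this ρ, so the same power.
- ANCOVA: SD* = 13.42, SE = 3.080, power = Φ(3.247 − 1.96) = 90.1%.

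**Step 3: power of the rule itself.** Simulation, 200,000 trials per setting, 38 per arm, t tests; ANCOVA replaces the unadjusted test only when baseline p < 0.05, which happened in about 5% of trials. These powers run up to about one point below the formula, which uses the normal approximation.

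| ρ | Always ANCOVA | Rule, follow-up scores | Loss | Rule, change scores | Loss |
|---|---|---|---|---|---|
| 0.3 | 82.5% | 79.6% | 2.9 | 66.4% | 16.1 |
| 0.5 | 89.0% | 80.2% | 8.8 | 80.4% | 8.6 |
| 0.6 | 93.2% | 80.8% | 12.4 | 88.2% | 5.0 |
| 0.7 | 97.2% | 81.3% | 15.9 | 95.2% | 2.0 |

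ANCOVA has the higher power in every row, but the loss runs in opposite directions for the two outcome forms. If 15.5 is instead read as the SD of the change score, formula power is 80.3% unadjusted, against 90.1% for ANCOVA at ρ = 0.5 and 86.2% at ρ = 0.7.

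**Step 4: overall type I error of the rule.** Follow-up scores: 4.7%, 4.4%, 4.1% and 3.6% at ρ = 0.3, 0.5, 0.6 and 0.7. Change scores: 4.0%, 4.4%, 4.5% and 4.6%. None exceeds 5%.

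**Step 5: type I error given the baseline imbalance.** These figures are from the same simulation. In the last two columns the baseline |t| lies between 1.5 and 1.99, so the rule does not adjust.

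| ρ | Follow-up, baseline abs. t < 0.5 | Change, abs. t < 0.5 | Follow-up, abs. t 1.5–1.99 | Change, abs. t 1.5–1.99 |
|---|---|---|---|---|
| 0.5 | 2.6% | 2.6% | 10.4% | 10.3% |
| 0.6 | 1.7% | 3.0% | 12.0% | 9.0% |
| 0.7 | 0.9% | 3.5% | 13.2% | 8.1% |

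ANCOVA stays at 4.9 to 5.3% in all these cells.

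At a single point, given baseline z, the unadjusted statistic under the null is N(cz, 1 − c²), with c = ρ for follow-up scores and c = −√((1 − ρ)/2) for change scores. At z = 1.9 and ρ = 0.6:

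- Follow-up: mean 1.14, SD 0.8, so P(Z > (1.96 − 1.14)/0.8) = P(Z > 1.025) = 15.3%.
- Change: mean 0.85 in absolute value, SD 0.894, so P(Z > 1.241) = 10.7%, plus 0.1% from the other tail, about 11%.

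The 8 to 15% is thus the band averages together with this one point. It shows the size of the effect and is not a bound.

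**The case against.** **The power loss is not a known property of this trial.** A reader might infer a fixed loss of 10 to 17 points. That range arises only for unadjusted follow-up scores at ρ of 0.5 to 0.7 with a back-solved SD, while the Outcomes section speaks of change. On change scores at the same correlations the loss is about 9 down to 2 points. This objection stands: only a range with its assumptions can be given. The planned multiplicity correction moves the range again. At alpha 0.025 and ρ = 0.5, formula power is 84.3% with ANCOVA against 71.6% unadjusted, a gap of 12.7 points.

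**The baseline is not ignored when the test is non-significant.** A reader might infer that the baseline score drops out of about 95% of trials. A change score uses it every time, and the article does not say whether the analysis of variance includes the baseline visit. This stands too, but an unadjusted change score over-corrects for baseline whenever ρ is below 1, so the conditional error and some power loss remain.

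**The trigger is not stated.** A looser threshold than 5% would bring more adjustment and a smaller loss. That is true, but the choice of model would still follow from the data. Blinding the analyst to group does not change this.

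**False positives are not inflated.** A reader might infer that the two-step rule breaks its nominal level upwards. Step 4 shows that it is slightly conservative overall, and under randomisation the unadjusted estimate is unbiased on average. The fault is conditional, and a baseline |z| between 1.5 and 1.96 arises in only about 8% of trials: 2 × (0.975 − 0.933) = 0.084.

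**The 38 per arm is a working figure.** The stated primary analysis is by intention to treat, with completers as a sensitivity analysis.

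**The Discussion is not at fault.** Its remark, "Randomization has been considered to help achieving a balance in sociodemographic, as well as risk factor profile", is correct and is no evidence of a defect.

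**Conclusion.** The point holds in a limited form. The article positively states a rule in which a baseline test guides adjustment, so this is not a detail left to an unseen analysis plan. The rule is inferior to always adjusting in every setting examined.

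Its cost is roughly 2 to 16 points of power, conditional on the assumed SD, correlation, trigger and number analysed, and on the form of the outcome. Overall type I error is about 4 to 5%. At correlations of 0.5 to 0.7 it rises to about 8 to 15% when the baseline imbalance is sizeable but not significant, where ANCOVA keeps 5%.

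The documents do not support a claim of general false-positive inflation or a single figure for lost power. The change should be made as a free improvement; the trial's validity overall does not hang on it.

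**What to change.** Replace the two-step rule in the Statistical analysis section with a prespecified one. Every primary comparison, for each scale and each time point, adjusts for the visit-1 score of the same scale, whatever the observed imbalance. This can be done by ANCOVA at each visit or with baseline as a covariate in a repeated-measures model.

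State that baseline tests do not determine the model. Baseline data may be shown by arm descriptively. If tests are still printed they do no inferential harm once the model is fixed.

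The cost is a sentence or two of wording, settled before the data are analysed. It needs no extra data, visits or participants, since both scales are already collected at visit 1 in both arms.

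### Analysis of variance is a poor vehicle for an intention-to-treat primary analysis with 30% expected loss: unless scores are imputed, it uses completers or available cases only

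*Protocol article*

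**What the plan says.** All four elements are in the protocol article.

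- Method (Statistical analysis): "The numeric outcomes will be analysed using analyses of variance". Whether this means one repeated-measures analysis or a separate analysis at each visit is not stated.
- Principle (Statistical analysis): "The primary analysis will be by intention to treat". No rule for missing scores accompanies it, and imputation is neither named nor excluded.
- Sensitivity (Statistical analysis): "As sensitivity analyses, completers of all assessments will be analysed separately". No other sensitivity analysis is named.
- Expected loss (Sample size): "the sample should be of 54 subjects in each group with an estimated loss of 30% during follow-up". The loss is not split by arm or visit.

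The Outcomes section defines the primary outcome as change in positive mental health and in caregiver burden at months 1, 3 and 6. The Statistical analysis section also provides for adjustment where baseline scores turn out to be imbalanced.

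**The concern.** Intention to treat asks that everyone randomised count in the comparison. Analysis of variance has no mechanism for a participant without a score. With almost a third of participants expected to be lost, the named method and the named principle fit together only if something further, such as imputation, is added.

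Two things are at stake. If participants who do badly leave one arm more than the other, the remaining groups are no longer comparable and the estimated effect shifts. And a completers analysis cannot reveal that shift, because it either repeats the primary analysis or restricts it further.

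Different loss in the two arms is possible here. The trial is open, and only one arm is asked to do a daily task. The article does not say that such loss is expected.

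**Working it through.** **1. The plan's own figure.** With n/(1 − loss), 54 per arm leaves 54 × 0.70 = 37.8, about 38. The stated inputs are "alpha risk of 0,05 and beta risk of 0,2" and "a difference greater than or equal to 10", with no SD. Solving n = 2(z₁ + z₂)²SD²/10² backwards for a two-sided test gives SD = 10 × √(38/2)/(1.960 + 0.842) = 15.6, or 15.4 with n = 37. If the inflation was n × 1.3, the SD is about 16.2 to 16.4; with a one-sided test it is about 17.3 to 18.4. So 54 is attainable but cannot be confirmed. At SD 15.5, 38 per arm gives about 80% power: the 30% loss is covered for precision, but not for bias.

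**2. Who enters each analysis if nothing is imputed.** Assume three follow-ups and even monotone loss, so the share retained per visit is 0.70^(1/3) = 0.888.

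| Analysis | Visit 1 of 3 | Visit 2 of 3 | Visit 3 of 3 |
|---|---|---|---|
| Repeated-measures ANOVA (listwise deletion) | 38 | 38 | 38 |
| Separate ANOVA per visit | 54 × 0.888 = 48 | 54 × 0.888² = 43 | 54 × 0.70 = 38 |
| Completers (sensitivity) | 38 | 38 | 38 |

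The first and third rows are the same people. The second row matches the third only at the last visit.

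**3. Bias at the last visit.** The documents give no SD, correlation or loss pattern, so these are assumptions: SD 15.4, between-visit correlation 0.6, 54 per arm, 4,000 replicates, true difference 0. Loss occurs after month 1. Full dependence means that the odds of loss multiply by e for each SD worse at month 1. The analysis compares final scores among those observed.

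| Loss pattern | Bias (points) | Two-sided type I error |
|---|---|---|
| Random, 35% app and 25% control | about 0 | not inflated |
| Full dependence in both arms, 30% each | 0.0 | 5% |
| Full dependence in both arms, 35% and 25% | 0.8 | 5% |
| Half dependence, app arm only | 1.5 | about 7% |
| Full dependence, app arm only, 35% and 25% | 2.7 | 11 to 12% |
| The same, with baseline adjustment | 1.1 to 1.2 | 6.8% |

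In the 2.7-point case the standard error is about 3.5, a shift of 2.7/3.5 = 0.77 standard errors. With a true difference of 10, the completer estimate is 12.7. An analysis that also uses the baseline and month-1 scores gives 10.0, and 0.0 when the true difference is 0.

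**4. Completers against available cases.** A large-sample run (SD 15.5, 30% monotone loss, app-arm loss depending on the previous score at −0.7 log-odds per SD, random loss in control, true difference 0) gives available-case differences of 0.7, 1.4 and 2.0 at the three follow-ups, and completer differences of 2.4, 2.5 and 2.0. With 40% against 20% loss and the same dependence in both arms, they are 0.5, 0.9 and 1.5, and 1.8, 1.7 and 1.5. A deliberately extreme pattern, with low scorers leaving one arm and high scorers leaving the other, reaches 4.0 at the last visit; I leave it out of the range.

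**5. Change scores.** The Outcomes section speaks of change. In the 2.7-point case, change-score ANOVA shows about 0 bias at the last visit. If app-arm loss depends instead on lack of improvement from baseline to month 1, change-score completer ANOVA is biased by about 2.0 at the last visit and 4.0 at month 1. Baseline adjustment leaves 1.2 at the last visit; using baseline and month-1 scores gives 0.0 there.

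**The case against.** The strongest reply is that the text does not say that anyone is dropped. It leaves the form of the analysis of variance open and does not rule out imputation. Setting completers apart as a sensitivity analysis implies a wider primary set. A journal article commonly leaves the missing-data rule to the full protocol or analysis plan, which is not shown. All of that stands, and the absence of such a rule is not the point made here. The point is that the method the article does name cannot by itself deliver the principle it names, and that a better one is available in the same software.

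It is also fair to say that the larger biases come from chosen scenarios. The assertion that caregivers who gain nothing are the likeliest to stop answering has no source in the article. The remark in the Follow-up section about no direct follow-up concerns the app; the scales are collected at visits in both arms, so leaving the app is not the same as missing an assessment. The possible baseline adjustment would also more than halve the worst case. These points limit the size of the concern, but they do not make analysis of variance a good choice with 30% loss.

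**Conclusion.** The point holds conditionally. Without imputation, the primary analysis is a completers analysis under repeated-measures ANOVA, or an available-case analysis under per-visit ANOVA, and in either form it coincides with the sensitivity analysis at the last visit if loss is monotone. In that situation the sensitivity analysis tests nothing at the last visit, or at any visit under the repeated-measures form.

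The possible last-visit bias is about 0 to 2.7 points against a planned difference of 10, and about 1.1 to 1.2 in the worst case with baseline adjustment. This rests on an assumed SD of about 15.4, a correlation of 0.6 and the loss patterns listed.

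A reader might infer that the intention-to-treat analysis certainly collapses to completers, or that the app's effect will be inflated with a type I error near 12%. The documents support neither. The first depends on an ANOVA form and an absence of imputation that the article does not settle. The second needs outcome-related loss that differs between arms, and 30% loss alone does not produce it. This is a cheap and worthwhile improvement to the stated method, not a demonstrated bias.

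**What to change.** For the two primary scales, replace analysis of variance with a linear mixed model for repeated measures (SPSS MIXED) on all randomised participants with any follow-up score. Include arm, visit, arm by visit and baseline score, and report the arm contrast at months 1, 3 and 6. Keep the completers analysis as supplementary only. Add one sensitivity analysis that departs from missing at random, for example delta-adjusted imputation; this is a reasonable supplement and not the core of the change.

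If analysis of variance is retained, state its form and how missing scores enter the intention-to-treat analysis.

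The cost is a change of wording and slightly more analysis work in software already named, with no new data. The downside is that the primary model then relies on missing at random, and a participant lost before any follow-up score still contributes nothing to it. The choice should be settled before the data are analysed.

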## Discussion

This study will evaluate whether positive mental health improves, and burdens of care reduces on caregivers. One strength of this study is its robust design and follow-up assessment allowing the evaluation of long-term effects of the intervention. However, one of its limitations is its open design. The intervention cannot be masked; both patients and nurses in the experimental and control group will be aware that they are participating in a positive mental health intervention. This could affect to the success or failure of the intervention and could introduce bias. Randomization has been considered to help achieving a balance in sociodemographic, as well as risk factor profile. A blinded researcher will be in charge of analysing the data.

Among the strengths of the study, there is that this clinical trial has the potential to provide a validated tool to use with caregivers. A tool which could be useful to increase positive mental health. This could benefit the caregiver and even the caretaker. In addition, it has potential to decrease burdens of care. If its effectiveness is proved, this tool can be adapted to multiple frameworks.

## Data Availability

The study status is ongoing. Data will be available when the study ends (31/12/2019).
